###### Secondary outcomes

2.1.5.1.2

GPS-derived mobility-related activities, including maximum distance traveled from home (km), daily step count (steps/day), and area of the convex hull [km^2^] (i.e., the minimum bounding geometry enclosing all the GPS loggings for each participant and the maximum area in which the participant engaged in activities), and GPS-derived quantity of out-of-home activities including number of trips (to out of home locations), homestay ratio (%), and time out of home (minutes) will be measured using smartwatch GPS data (40).

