Participant tracking method (wear time)	Wear time each day will be determined based on the number of heart rate observations for the day; this is a more reliable indicator of wear time compared to start/stop times for daily heart rate samples as there can be gaps during the day where no heart rate data are captured (e.g., due to no/low battery, participant remove watch for bathing/swimming). Examination of the smartwatch data collected in the pilot study showed that heart rate data was captured consistently in accordance with the developer’s specified sample frequency (1 Hz).
Quality control checks	Heart rate data will be checked for validity (i.e., no negative or 0 readings), and invalid data will be removed prior to analysis. Duplicate samples (i.e., samples having an identical time stamp) will also be removed. Based on the examination of the smartwatch data from the pilot study, very few invalid samples were found (e.g., <0.1% of the data). Step count data will be checked for reasonableness (e.g., unreasonably high values for target population) and obvious errors (e.g., negative numbers for step counts indicating an invalid reading). The smartwatch captures cumulative steps for the entire wear time for the time point (seven days for participants the comply with the protocol). Ending step counts for a given day will be matched with starting step counts for the next day, and discrepancies will be identified and appropriately resolved. Based on the examination of the smartwatch data collected in the pilot study, step counts were reasonable with no obvious errors. GPS data are challenging to validate, especially for this target population, many of which live in apartment dwellings where a GPS signal is often obstructed, and satellite coverage can be variable/unreliable. The level of accuracy (in meters) will be determined based on the distribution of the values, density for the study area, needed accuracy to distinguish between locations etc. Invalid data will be removed from the dataset prior to analysis.
Compliance criteria	For step count and GPS-related measures, all days with at least 6+ hours of wear time (up to a maximum of 7 days/participant/time point) available data will be used in the calculations (i.e., if participants only have data for 5 of the 7 days for a given time point, these days will be used to generate measures, including averages, distance measures, trips).

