Summary variables/categorizing data	1) Heart rate data will be used to calculate the primary outcome (MVPA in minutes/day). Heart rate samples will be categorized as vigorous/moderate/light using the algorithms described in Section 2.1.5.1. 2) Step count data will be used to calculate a secondary outcome measure related to mobility. The TicWatch captures the total step count for each day the watch is worn. The average daily step count for each time point (t_1_, t_2_, t_3_) will be calculated by averaging across the wear period for each time point (seven days for participants that comply with the protocol). 3) GPS data will be used to calculate a variety of distance-related measures (e.g., number of trips, maximum distance from home, homestay ratio). The algorithms used to generate the measures using GPS data will be implemented in R version 4.4.1 and based on the R Markdown guidance document provided by Muller and colleagues (94).

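### GPS extent measures are computed over however many days are valid, so maximum distance and convex hull area depend on wear as well as on mobility

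*Protocol article*

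**What the plan says.** The Compliance criteria row of Table 3 (Section 2.3.1.1, Smartwatch data) sets one rule for step count and GPS measures: "all days with at least 6+ hours of wear time (up to a maximum of 7 days/participant/time point) available data will be used". For an incomplete week it adds: "if participants only have data for 5 of the 7 days for a given time point, these days will be used to generate measures". It names distance measures and trips among these, along with averages. It gives no minimum number of valid days.

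Section 2.1.5.1.2 (Secondary outcomes) lists the measures. One group is "maximum distance traveled from home (km), daily step count (steps/day") and a convex hull defined as "the minimum bounding geometry enclosing all the GPS loggings for each participant and the maximum area in which the participant engaged in activities". The other is "number of trips (to out of home locations), homestay ratio (%), and time out of home (minutes"). Only step count carries a per-day unit.

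The Summary variables row of Table 3 says that step count is obtained by "averaging across the wear period for each time point (seven days for participants that comply with the protocol"). It makes no such statement for the GPS measures.

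The model in Section 2.3.3.2 has fixed effects for baseline value, arm, time and their interaction, with random effects for site and participant. It has no term for valid days or wear time. Multiple imputation in the same section is for missing values.

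**The concern.** Using all available days is sound for an average: fewer days make it noisier but do not shift it, provided the lost days are like the others. A maximum or a hull behaves differently, because each added day can only leave it unchanged or enlarge it. A person with three valid days is then compared with a person with seven on a quantity that partly measures how long the watch was worn.

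A hull computed from three days enters the model as an observed value. The mixed model takes it at face value and imputation leaves it alone. If the arms differed in valid days at a follow-up visit, part of that difference would appear as a difference in community mobility with no change in where people went.

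**Working it through.** The article gives no distribution of valid days and no GPS effect size or SD, so there is no figure of its own to reproduce. The check is of the mechanism.

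**Direction (no assumption needed).** For any subset S of the seven days:
- max over S ≤ max over 7 days
- hull area over S ≤ hull area over 7 days
- total over S ≤ total over 7 days

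**Size per person (assumed distributions, unchanged behaviour).** Ratio of the expected value on k days to that on 7 days:

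| Measure | Assumption | k = 5 | k = 3 |
|---|---|---|---|
| Total trips or minutes, if totals | constant daily rate, k/7 | 5/7 = 0.71 | 3/7 = 0.43 |
| Maximum distance | lognormal daily maximum, log-SD 0.5 | 0.92 | 0.79 |
| | log-SD 1.0 | 0.85 | 0.66 |
| | log-SD 1.5 | 0.80 | 0.56 |
| Hull area | home plus two heavy-tailed (t, 4 df) points a day | 0.75 | 0.42 |
| | home plus Poisson(1.5) destinations a day, log-SD 0.5 | 0.73 | 0.41 |
| | same, log-SD 1.0 | 0.66 | 0.33 |

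So 5 rather than 7 days lowers totals by 29%, maximum distance by 8–20% and hull area by 25–34%. The hull models draw new destinations every day. People who return to the same places would lose less area.

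**From person to arm.** An arm difference depends on the gap in mean valid days, which the documents do not give. Take one arm at 6 valid days and the other at 5:
- totals: 5/6 = 0.83, a 17% deficit
- maximum distance: 0.917/0.962 = 0.95 (log-SD 0.5) to 0.802/0.904 = 0.89 (log-SD 1.5), a deficit of 5–11%
- hull area: 0.727/0.867 = 0.84 to 0.660/0.831 = 0.79, a deficit of 16–21%

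With a half-day gap, totals differ by 1 − 5.5/6 = 8%. With no gap, the expected difference is nil.

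**Effect on a test, for trips if they are totals.** Inputs from the article are 250 or 500 participants and 80% retention at 6 months (Section 2.1.7), so 0.8 × 125 = 100 or 0.8 × 250 = 200 completers per arm. Assumed inputs are 1.5 trips a day, between-person CV 0.5, and a mean of 6 valid days in one arm. The test is a two-sided 5% t-test at one timepoint with no true effect.

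| Gap in mean valid days | Rejections, total trips (N = 250; N = 500) | Rejections, trips per valid day |
|---|---|---|
| 0 | 4.9%; 5.2% | 5.2%; 4.8% |
| 0.5 | 16.8%; 26.3% | 5.5%; 5.3% |
| 1.0 | 50.5%; 80.4% | 4.6%; 5.7% |

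Dividing by valid days removes the problem for a count. It does not repair a maximum or a hull, which do not grow in proportion to days.

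**The case against.** Several points on the other side stand.

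- **Trips and time out of home.** They have no stated period. The Compliance row mentions averages, and the algorithms follow a cited guidance document that is not shown. They may well be daily averages, so the 29% figure and the test simulation apply only if they are totals. The text leaves much less room for the hull, which is defined over all logged points, or for the maximum.
- **A fall in wear common to both arms.** A reader might infer that any drop after baseline biases the result. The model contrasts arms at follow-up with baseline as a covariate, so a common fall largely cancels when there is no true effect. It mainly distorts within-arm change and adds noise.
- **Direction.** A reader might infer that unblinded controls will wear the watch less and that this favours the intervention. The documents report no wear by arm. Both arms receive the same mailing, instructions and gift cards, although the cards are paid for interviews and not for wear.
- **Baseline wear as an entry condition.** A reader might infer this from randomisation following return of the watch (Section 2.1.6). No minimum number of valid days is required there.
- **Stakes.** Community mobility is also measured by the Life Space Assessment, a telephone questionnaire that does not depend on the watch. The GPS measures have no row in Table 4.

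What survives is the rule itself. It is stated, it names distance measures and trips, it has no minimum, and nothing later in the analysis corrects it.

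**Conclusion.** The point holds for maximum distance from home and convex hull area, and conditionally for number of trips and time out of home. The direction of the effect of fewer days is certain. Its size rests on assumed distributions of daily travel. Bias in the arm comparison requires valid days to differ between arms, which is possible in an open-label trial but is neither documented nor signed by anything in the article. The outcomes concerned are secondary. MVPA and step count are averages per day and homestay ratio is a proportion, so none of them shrinks mechanically with fewer days. The rule should be changed because the correction is cheap and is best fixed before wear by arm is known.

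**What to change.** Revise the Compliance criteria row of Table 3 and the R derivation code:

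1. Define number of trips and time out of home per valid day.
2. For maximum distance and hull area, choose one basis in advance. Either average the daily values over valid days, or compute the wear-period value on a common, prespecified number of valid days (for example, averaged over random subsets of that size) and set participants below that number to missing. Adjusting for the number of valid days is an alternative, but a weaker one, because wear at follow-up is measured after randomisation.
3. Report the number of valid days by arm and timepoint.

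No new data are needed. Under the common-number option, some participants become missing on the extent measures and pass to the mixed model and imputation already planned. How many cannot be told from the article. Under the daily option, a daily maximum or daily hull measures a somewhat different construct from extent over the week. Neither option deals with hours within a day: a six-hour and a fourteen-hour day still count alike, so reporting wear hours alongside valid days would help.

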##### Assessment tools data

2.3.1.2

Study data were collected and managed using REDCap electronic data capture tools hosted at McMaster University. REDCap (Research Electronic Data Capture) is a secure, web-based software platform designed to support data capture for research studies, providing (1) an intuitive interface for validated data capture; (2) audit trails for tracking data manipulation and export procedures; (3) automated export procedures for seamless data downloads to common statistical packages; and (4) procedures for data integration and interoperability with external sources.

Data will be directly entered into REDCap to track numbers of potential participants who contacted team based on interest in study, screened, eligible, recruited (eligible and provided informed consent). Data on weekly group-based program delivery fidelity and participant attendance will be captured by the Program Coordinator and entered into REDCap; Genie® data (e.g., social network, interests, community resources recommended) will be captured within Genie®, while data about participation in 1:1 sessions will be captured in REDCap. Mid- and end-of-program satisfaction surveys will be collected at the group program by the Research Coordinator as part of a site visit. These surveys are comprised of 5-point Likert-scale questions to explore overall impressions, satisfaction, and usefulness of program components/activities, followed by open-ended short text-answer questions to explore feedback on what contributed to their retention, perceived benefits/impact, barriers/challenges and future program enhancements.

Quantitative data will be collected from participants at each timepoint by independent research assistants blinded to allocation. Virtual data collection is expected to reduce participant burden and completion time, limiting the need to travel for both participants and research staff.

Qualitative data will be collected from a subset of intervention group participants using 1:1 semi-structured virtual interviews (by Zoom or telephone based on participant preference). Following the completion of each cohort, a subset of 5–6 participants per site will be identified to reflect a diversity of perspectives with respect to age, gender, socio-economic status, living status (alone or with others), and high vs. low engagement rates with program. Focus groups will also be conducted annually with the Hamilton intervention team to explore implementation determinants, adaptations and sustainability/scalability (with 1:1 interviews offered for those unable to attend a scheduled focus group). Separate focus group interviews will be conducted with the Mandarin-speaking and Toronto intervention teams. As part of the SGC and CAB meetings, questions will be posed to explore implementation, any adaptations necessary for successful research and program implementation in each neighborhood, as well as input into perceived sustainability and scalability at the final CAB meeting in each area; meeting notes will capture SGC and CAB input.

#### Data management

2.3.2

All information will be kept confidential and study IDs will be used whenever data are coded. Records for this study will be in electronic (i.e., initial demographic and medical information, and questionnaires) and in paper forms. The electronic data from questionnaires will be housed on REDCap® through McMaster University network servers; the electronic Study Key (participant identification and contact information) will be stored in a file on McMaster University network servers and accessed through a password-protected computer. Once received, paper documents will be kept in a locked cabinet on campus. Only research team members will have access to data.

The Genie® System is provided as a hosted service and all data will sit on a server in Canada. We will use Microsoft (MS) Azure for hosting the data. The data will be backed up in Canada using MS Azure. MS Azure does not connect with any other services prior to Canadian servers. MS Azure’s encryption protocols erect barriers against unauthorized access to the data, including two or more independent encryption layers to protect against compromises of any one layer. MS Azure policies include the adoption of the international code of practice for cloud privacy, ISO-IEC 27018.

The smartwatch will be equipped to obtain GPS signals from the satellites to determine position (longitudinal and latitudinal coordinates). Only the coordinates for the destination information will be used to define parameters such as distance traveled. All GPS data will be encrypted with a secure password to prevent unwanted access in the case of loss of the device.

Users from the public register for Voice provide both their contact information and personal information (e.g., age, postal code, gender). The privacy and data storage policies have been reviewed and approved by the privacy and legal offices of both McMaster University and the University of Newcastle. Voice has rigorous guidelines in place to both protect data and ensure there is a rapid response in the unlikely event of a security breach. Data Security Protocols were reviewed and approved as part of the platform’s HiREB Application (#14929) and were also reviewed and approved by McMaster University’s Privacy Officer and Legal Office before the platform’s licensing agreement was signed.

#### Analysis methods

2.3.3

##### Baseline socio-demographic characteristics

2.3.3.1

Descriptive statistics will be used to compare treatment groups on baseline socio-demographic characteristics. Conventional statistical comparison of baseline characteristics of treatment groups (e.g., covariate imbalance *p* values) will not be reported; CONSORT 2010 guidelines discourage this in alignment with the widespread consensus that these methods are not appropriate to establish significant group differences in RCTs (69, 70).

##### Effectiveness evaluation

2.3.3.2

Table 4 summarizes the outcomes/hypotheses/analyses pertaining to the primary, secondary, sensitivity and subgroup analyses. Treatment groups will be compared for the change from baseline for the primary and all secondary outcomes using a linear mixed model (LMM) or generalized LMM (GLMM). Mixed effects models are preferred in repeated measures clinical trials as these models handle missing data, more complex designs, and non-continuous outcomes (71). Generalized estimating equations (GEE) is another analytical option, although it is less often used due to its missing-completely-at-random (MCAR) assumption (72, 73). LMM/GLMM models generate estimates that are valid when the data are missing at random (MAR), which is recommended for the primary analysis in clinical trials as it is more reasonable than MCAR and less complex compared to missing-not-at-random (MNAR) modeling methods (74). GEE and LMM/GLMM all produce similar results if observed data are not related to missing data (73).

**Table 4 tab4:** Quantitative outcomes, hypotheses and methods of analyses.

Objective	Outcome, data type	Hypothesis^a^	Method of analysis^b^^,^^c^
Primary outcome analysis	Moderate-Vigorous Physical Activity (MVPA)	I, compared to C, shows increase in MVPA from baseline to 6 months	LMM/GLMM, REML estimation of model parameters, LSM (95% CI) for treatment group differences
Secondary outcome analysis	Life Space Assessment (LSA)	I, compared to C, shows increase in LSA score from baseline to 6 months	LMM/GLMM, REML estimation of model parameters, LSM (95% CI) for treatment group differences
	Short Form Health Survey, 12 Questions (SF-12): Physical Component Summary (PCS); Mental Component Summary (MCS)	I, compared to C, shows increase in PCS & MCS score from baseline to 6 months	LMM/GLMM, REML estimation of model parameters, LSM (95% CI) for treatment group differences
	EuroQoL 5 Dimension (EQ-5D): Today’s health; Mobility; Self-care; Usual activities; Anxiety/Depression; Pain	I, compared to C, shows increase in EQ-5D (today’s health, mobility, self-care, usual activities) and decrease in EQ-5D (pain, anxiety/depression) from baseline to 6 months	LMM/GLMM, REML estimation of model parameters, LSM (95% CI) for treatment group differences
	Patient Health Questionnaire (PHQ)	I, compared to C, shows decrease in PHQ score from baseline to 6 months	LMM/GLMM, REML estimation of model parameters, LSM (95% CI) for treatment group differences
	Physical Activity in Seniors (PASE)	I, compared to C, shows increase in PASE score from baseline to 6 months	LMM/GLMM, REML estimation of model parameters, LSM (95% CI) for treatment group differences
	Outcomes Expectation for Exercise (OEE)	I, compared to C, shows increase in OEE score from baseline to 6 months	LMM/GLMM, REML estimation of model parameters, LSM (95% CI) for treatment group differences
	De Jong Gierveld Loneliness Scale	I, compared to C, shows decrease in loneliness score from baseline to 6 months	LMM/GLMM, REML estimation of model parameters, LSM (95% CI) for treatment group differences
	Collective Efficacy of Networks (CENS)	I, compared to C, shows increase in CENS score from baseline to 6 months	LMM/GLMM, REML estimation of model parameters, LSM (95% CI) for treatment group differences
	Seniors in the Community Risk Evaluation for Eating and Nutrition (SCREEN II)	I, compared to C, shows decrease in SCREEN II score from baseline to 6 months	LMM, REML estimation of model parameters, LSM (95% CI) for treatment group differences
	Sense of community belonging	I, compared to C, shows increase in community belonging score from baseline to 6 months	LMM/GLMM, REML estimation of model parameters, LSM (95% CI) for treatment group differences
	Resilience	I, compared to C, shows increase in resilience score from baseline to 6 months	LMM/GLMM, REML estimation of model parameters, LSM (95% CI) for treatment group differences
	Short food literacy	I, compared to C, shows increase in food literacy score from baseline to 6 months	LMM/GLMM, REML estimation of model parameters, LSM (95% CI) for treatment group differences
	Food security: Worry will run out of food; Ran out of food	I, compared to C, shows decrease in food security concern from baseline to 6 months	LMM/GLMM, REML estimation of model parameters, LSM (95% CI) for treatment group differences
	Health and Behavior Assessment (HABiT): Concern (High Blood Pressure, Diabetes); Understanding (High Blood Pressure, Diabetes); Importance (Fruit/Veg, Salt, Physical Activity); Confidence (Improving Health Activities)	I, compared to C, shows decrease in concern and increase in understanding (high blood pressure/diabetes), importance (fruit/veg, salt, physical activity) and confidence (improving health activities) of concern baseline to 6 month	LMM/GLMM, REML estimation of model parameters, LSM (95% CI) for treatment group differences
Sensitivity analysis	Primary and secondary outcomes	Results from pooled analysis of multiple-imputed data sets will be consistent with original primary and secondary analyses	Explores impact of missing data using multiple imputation by chained equations (MICE), predictive mean matching, imputation by treatment group; employs modeling approach used in main analyses (i.e., LMM/GLMM, REML, LSM & 95% CIs)
Subgroup analysis	Moderate-Vigorous Physical Activity (MVPA) by sex category (male, female, other)	Treatment effect will be consistent across sex categories	Performed if overall treatment effect observed; employs modeling approach used in main analyses (i.e., LMM/GLMM, REML, LSM & 95% CI); separate models run for each category, interactions test (treatment group × sex) provided
	Moderate-Vigorous Physical Activity (MVPA) by 10-year age categories	Treatment effect will be consistent across age categories	Performed if overall treatment effect observed; employs modeling approach used in main analysis (i.e., LMM, REML, LSM & 95% CI); separate models run for each category, interactions test (treatment group × age) provided

a I = Intervention Group, C = Control Group.

b LMM = linear mixed model, GLMM = generalized linear mixed model, REML = restricted maximum likelihood estimation, LSM = least squares means (=model predicted means), CI = confidence interval.

c LMM/GLMM models will include the following fixed effects: outcome value at baseline, time (categorical), treatment group (categorical), and treatment × time interaction (categorical). Random effects for participants and sites will include either random intercepts, or the more complex model (random intercepts and random slopes) if suggested by spaghetti plots and fit statistics.

